## Abstract

**Background:**

Online information retrieval systems have the potential to improve patient care but there are few comparative studies of the impact of online evidence on clinicians' decision-making behaviour in routine clinical work.

**Methods/design:**

A randomized controlled parallel design is employed to assess the effectiveness of an online evidence retrieval system, Quick Clinical (QC) in improving clinical decision-making processes in general practice. Eligible clinicians are randomised either to receive access or not to receive access to QC in their consulting rooms for 12 months. Participants complete pre- and post trial surveys.

Two-hundred general practitioners are recruited. Participants must be registered to practice in Australia, have a computer with Internet access in their consulting room and use electronic prescribing. Clinicians planning to retire or move to another practice within 12 months or participating in any other clinical trial involving electronic extraction of prescriptions data are excluded from the study.

The primary end-points for the study is clinician acceptance and use of QC and the resulting change in decision-making behaviour. The study will examine prescribing patterns related to frequently prescribed medications where there has been a recent significant shift in recommendations regarding their use based upon new evidence. Secondary outcome measures include self-reported changes in diagnosis, patient education, prescriptions written, investigations and referrals.

**Discussion:**

A trial under experimental conditions is an effective way of examining the impact of using QC in routine general practice consultations.

## Background

Several studies have shown that clinicians have many unanswered questions during clinical encounters which may impact on the quality and outcomes of decisions made. Depending on measurement techniques used to estimate the frequency of questions and the clinical setting, clinicians have anywhere between 1 and 6 questions per patient encounter and answers are pursed for only about 30% to 55% of questions [1-4]. Improving access to clinical evidence through the implementation of evidence retrieval systems is one way of supporting information seeking in routine care [5]. Easy access to up-to-date evidence at the point of care may be more effective than other interventions aimed at improving clinicians adoption of evidence-based practice such as CME, distribution of clinical guidelines, clinical detailing, etc.

The effect of implementing information retrieval technology in routine clinical settings and its impact on clinicians' decision-making has not been extensively investigated. A 2005 review found that on average one in three searches for information were associated with a positive impact on decision-making, however in 73% (19 of 26) of the studies examined in this review, the impact was self-reported by clinicians using the system [6]. Assessments of evidence retrieval systems have relied principally on post study surveys. Only a small number have directly measured use in clinical settings and in most cases patterns of searching and clinical usefulness of information retrieved could not be identified.

There are few comparative studies of online evidence retrieval technology in routine clinical settings. A Finnish study found no difference in compliance with recommendations between computerised and paper-based clinical guidelines among newly qualified physicians [7]. In another study involving fourth year medical students, participants reported that access to information on a handheld computer encouraged use of information, improved learning and increased confidence in decision-making [8]. However, the effect of information retrieval technology on clinicians decision-making process and impact upon patient outcomes has not been assessed.

We are conducting a randomised controlled trial (RCT) to investigate the effectiveness of an information retrieval system called Quick Clinical (QC) in general practice [9]. The feasibility of the QC system was demonstrated in a previous clinical trial, detailed results of this study are reported in a separate paper [10]. Overall, 193 clinicians used the online evidence system to conduct on average 8.7 searches per month. The majority of these searches were conducted from consulting rooms (81%) during office hours. The most frequent searches conducted related to questions about diagnosis (40%) and treatment (35%). Search subjects included a broad spectrum of diseases, including common conditions such as asthma, diabetes and hypertension. In this paper we describe the design and proposed analysis of an RCT to evaluate the effectiveness of using QC in routine general practice consultations.

## Methods

### Study aims

The aim of this trial is to assess the effectiveness of an online evidence retrieval system (QC) in improving clinical decision-making processes in general practice.

The specific hypotheses to be tested in this study are that:

1. Online evidence systems are clinically acceptable and will be used by clinicians in 'real world' general practice settings.

2. Online evidence systems are effective in changing clinical decision-making behaviour and result in measurable improvements in evidence-based prescribing decisions.

### Study design and setting

A randomized controlled parallel design is used to evaluate the effectiveness of QC.

#### Intervention

Participants are randomised to receive access to QC in their practice for 12 months. The system is available from a standard web browser e.g. Microsoft Internet Explorer, Firefox etc. (Figure 1). Each user has a personal username and password and completes an online tutorial about how to use the system. QC is based on the generic use of search filters specifically designed around the information needs of general practitioners (GP). Five types of search filters or "profiles" are available (disease aetiology, diagnosis, treatment, prescribing and patient education). Up to four keywords can be used to describe a clinical question. Clinicians search for information firstly by selecting a search filter to match their question type (e.g. diagnosis, treatment etc.) and then entering keywords to describe the query. For example, a clinician who encounters a 32-year old woman with a fourth presentation of pelvic pain in the last 6 months with ultrasound and swabs for infection all negative, may have a question regarding the social, psychological as well as biological causes of pelvic pain. The clinician could select the 'etiology' profile and enter 'pelvic pain', 'pathology' and 'psychosocial' as keywords (Figure 1). The search filters retrieve evidence from resources including Therapeutic Guidelines (a summarised evidence resource developed by Australian experts); the Merck Manual; Health Insite (a government funded health database); PubMed; MIMS (a pharmaceutical database); and a collection of relevant Australian guidelines identified by a panel of clinical experts. Users can also search each of these resources individually.

**Figure 1 F1:**
[figure not shown]
Quick Clinical user interface.

**Figure 2 F2:**
[figure not shown]
Screenshot of online feedback facility (questions after [16]).

#### Outcomes

The primary outcome measures are clinician acceptance and use of QC and the resulting change in decision-making behaviour. The data from our pilot study of QC involving 227 GPs showed that online evidence was sought in relation to both frequent and rare clinical conditions across a broad range of clinical areas [10]. This suggests that we are likely to see access to evidence having a broad impact across common and rare clinical decisions. The RCT will therefore examine prescribing patterns related to frequently prescribed medications where there has been a recent significant shift in recommendations regarding their use based upon new evidence. Examining the effect on management decisions in clinical areas where there is shifting evidence enables a hypothesis driven approach to determine the impact of online evidence on clinician behaviour.

The RCT will therefore focus on the changes in clinicians' prescribing patterns in Australian National Health priority areas identified by a panel of experts including chief investigators, associate investigators and general practitioners (Table 1). Non-pharmacological clinical management in these priority areas will also be examined e.g. referral for podiatry (diabetes management), spirometry (asthma), HbA1c testing (diabetes), cognitive behavioural therapy (CBT) for depression, dieticians for lipid disorder. In addition to changes in priority areas, prescribing patterns in response to new evidence of the effectiveness of new or existing treatments identified through reviews of literature and expert input will also be assessed. Secondary outcome measures to determine impact on decision-making behaviour include self-reported changes in diagnosis, patient education, prescriptions, investigations and referrals.

**Table 1 T1:** Clinical priority areas used to measure primary outcomes.

***Clinical area***	***Expected changes in intervention group***
Asthma	↓ short acting beta-agonists ↑ long-acting beta-agonists ↑ inhaled corticosteroids (decreased dose of steroids over time i.e. back titration or combinations of LABA & corticosteroids)
Depression	↑ SSRIs, ↑ SNRIs ↓ TCAs;
Hypertension	↑ diuretics ↓ other antihypertensives
Upper respiratory tract infection	↓ antibiotics and ↑ appropriate antibiotics
Immunisation/vaccination	Higher rate of immunization and closer compliance with schedule.
Lipid disorders	↑ Statins,
Type 2 Diabetes	↑ glitazones ↑ metformin ↑ insulin ↓ sulfonylureas
Non-inflamatory musculoskeletal including osteoarthritis	↑ paracetamol ↓ NSAIDs ↓ Cox-2 inhibitors

#### Ethical considerations

Ethical approval for the study was obtained from the University of New South Wales's Human Research Ethics Committee and subsequently ratified by Sydney University and the Royal Australian College of General Practitioners ethics committees.

The study is also recognised by the Royal Australian College of General Practitioners (RACGP) for its continuing medical education (CME) program. Education points are not directly linked to participants' use of QC, but to trial completion.

### Identification of eligible general practitioners

GPs who had a computer with Internet access in their consulting rooms and used electronic prescribing are recruited via a call for volunteers advertised in journals, newsletters and a clinician list-server. An overview of the trial process is shown in Figure 3. Volunteers are asked to register via a web page and to complete a short survey to determine their eligibility to participate in the study. The online registration gathers baseline data about the demographics of the sample including practice characteristics and computer use [see Additional file 1]. Eligibility and exclusion criteria are listed in Table 2. To participate in the study clinicians must be registered to practice in Australia; have a computer with Internet connectivity; and prescribe electronically. GPs who are planning to retire or move to another practice within 12 months or participating in other concurrent trials involving electronic extraction of prescription data are excluded from the study.

**Figure 3 F3:**
[figure not shown]
Overview of trial process.

**Table 2 T2:** Study inclusion and exclusion criteria.

***Inclusion criteria***
• general practitioners registered to practice in Australia
• use a computer with Internet access in consulting rooms
• use electronic prescribing
***Exclusion criteria***
• concurrent participation in other clinical trials involving electronic extraction of prescription data
• planning to retire or move within the next 12 months

Eligible GPs are randomly allocated to either the control or intervention group, each clinician is given a unique study identification code and the web address of QC is sent to eligible participants one week prior to commencement of the trial. Participants visiting the QC web site are given detailed information about the trial along with the participant information statement and the consent form. A revocation of consent form is also available online. Clinicians willing to participate complete the online consent form and a pre-trial survey which assesses information seeking habits and attitudes to information seeking during consultations [see Additional file 2]. A psychometric instrument used to classify clinicians' response styles to new information as seekers, receptives, traditionalists, or pragmatists is also administered as part of the pre-trial survey [see Additional file 3] [11].

### Data collection

The timing and content of study assessments are summarised in Table 5. Frequency and purpose of system use of QC are determined from automatically generated computer logs used to record details of each search including the search filter chosen, keywords entered, data sources accessed, user IP (Internet Protocol) address, date, time and duration of searches [see Additional file 4]. Users are asked to identify if the IP address is their home or consulting room. An online feedback facility within the QC user interface is used to record clinicians comments in context of specific searches that generate the feedback (Figure 2).

Participants in both the control and intervention group provide prescribing data in electronic format [see Additional file 5]. The data extraction process excludes all potentially identifying information such as patient name, address, gender, postcode, telephone number, Medicare number, progress notes, images (e.g. X-rays) and any data fields that could identify a patient, such as free text fields. Data for the study period (i.e. 12 months retrospective data plus 12 months of the intervention period) is electronically extracted from prescribing software using secure means without any intrusion on clinicians' work.

The prescription data extraction software and installation instructions are sent by email and also are made available online. The first data extraction (i.e. retrospective prescriptions data from the previous 12 months) is performed after installation of the extraction software at the start of the study. The second extraction is scheduled at 6 months and the final at 12 months. An uninstall program will remove all extraction software, created files and changes to profiles in clinicians' prescribing software. At the end of 12 months all participants complete a post-trial survey [see Additional file 6]. Participants attitudes to information seeking and responses to the psychometric instrument used in the pre-trial survey are repeated post-trial.

#### Randomisation, blinding and allocation concealment

Eligible GPs are stratified by gender and randomised to the intervention or control group using a computer generated random number sequence in randomly assigned blocks (max. block size 8) and online evidence allocation ratio of 1:1. For each level of strata, a random sequence of study group assignments is generated using a computerized random-number generator [12]. Each level of strata are numbered consecutively. Each doctor receives the next consecutive number in his or her stratum.

Since QC is a behavioural intervention it is not possible to blind participants to the intervention. However investigators are blinded to group assignment. The randomisation sequence is generated and clinicians are randomly assigned to two groups by a researcher from the Evaluation team of the Centre for Health Informatics. This individual is not directly involved in the study nor its analysis.

The group assignment is revealed to clinicians online only after they consent to participate in the study following completion of the pre-trial survey. To minimise contamination of control participants who might work closely with practitioners who are part of the intervention group, only one clinician is eligible to participate in the trial from each practice. In cases where there are multiple registrations from a single practice, only the first registrant is eligible to participate. Participants in the intervention group are asked not to share their QC access details with their colleagues.

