### Statistical analyses

All registered participants will have completed the pre-trial survey. The subset of the intervention group analysed for primary outcome will have completed the post-trial survey and provided prescribing data. Participants in intervention group who encounter technical difficulties in using QC will be excluded from this analysis (i.e. those who had the opportunity to use QC but did not do so will be included). All of the control group except those who did not provide prescribing data will be included in the primary analysis. As summarised in Table 5 the intervention and control groups will be compared for baseline differences in prescription patterns, case-mix and profile of participants. Using an intention to treat analysis adjusted data will be analysed to determine differences in prescribing patterns and non-pharmacological management in identified priority areas, and areas in which there have been recent changes in response to new evidence using a one-tailed binomial test for proportions. Self-reported changes in diagnosis, patient education, prescriptions, investigations, referrals will also be examined. Utilisation and outcome measures will be analysed relative to QC usage and patient load (e.g. by number of patients seen).

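### A GP can know the allocation before installing the extraction software and supplying prescribing data, so entry to the primary analysis can depend on it in either arm

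*Protocol article*

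**What the plan says.** All references are to the protocol article.

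- **Before disclosure.** Eligible GPs are randomised, and "the web address of QC is sent to eligible participants one week prior to commencement of the trial" (text after Table 2). On that site they read the trial information, consent and complete the pre-trial survey.
- **Disclosure.** "The group assignment is revealed to clinicians online only after they consent to participate in the study following completion of the pre-trial survey" (Randomisation, blinding and allocation concealment). The same section accepts that "it is not possible to blind participants to the intervention".
- **Supply of prescribing data.** "The prescription data extraction software and installation instructions are sent by email and also are made available online" (Data collection). The first extraction covers the previous 12 months and "is performed after installation of the extraction software at the start of the study". Further extractions follow at 6 and 12 months.
- **Analysis set.** For controls: "All of the control group except those who did not provide prescribing data will be included in the primary analysis". For the QC arm: "The subset of the intervention group analysed for primary outcome will have completed the post-trial survey and provided prescribing data". QC GPs with technical difficulties in using the system are also left out (Statistical analyses). The same section describes the approach with the words "Using an intention to treat analysis adjusted data will be analysed".

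**The concern.** Holding back the assignment until after consent and the survey protects those two steps from knowledge of the arm. It does not protect the later step that produces the outcome data. Installing the software is a voluntary act by the GP, and nothing in the text requires it, or receipt of the first extraction, before the group is shown. A GP who does not supply data is not analysed.

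If knowing the arm changes the willingness to install, and willingness is related to prescribing, the two analysed groups are no longer comparable as randomised, even before any effect of QC. Non-suppliers have no prescribing data at all, so a comparison of baseline prescribing among suppliers cannot show how they differed.

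**Working it through.** **1. Order of events.** The text names two conditions for disclosure: consent and the pre-trial survey. It places installation and first extraction at the start of the study, and the site for consent opens one week before that start. The list under Communication with participants puts the start of the trial ahead of the installation instructions, which fits the same order. No sentence states that installation follows disclosure. The firm statement is that nothing makes installation or extraction a condition for it.

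**2. What is collected before disclosure.** Registration demographics, practice characteristics, the pre-trial survey and the psychometric instrument. Baseline prescribing is the part that can come after.

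**3. Target effect (Sample size considerations).** 58.4 − 53 = 5.4 points, or 5.4/53 = 10.2% relative. The 100 GPs per arm cannot be reproduced, because the encounters per GP in Table 4 are not in the text. This point does not rest on that figure.

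**4. Spread between GPs.** From the stated ICC of 0.02 and the 53% rate: SD = √(0.02 × 0.53 × 0.47) = 0.0706, or 7.1 points.

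**5. Illustration A (assumed: 25% of controls and 10% of QC GPs do not install; propensity to install correlates 0.3 with the GP's underlying rate).** Shift in an arm's mean = r × φ(z_q)/(1 − q) × SD, where q is the fraction not installing.
- Control: 0.3 × 0.3178/0.75 × 7.06 = 0.90 points
- QC: 0.3 × 0.1755/0.90 × 7.06 = 0.41 points
- Net: 0.897 − 0.413 = 0.48 points; 0.48/5.4 = 9%

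With a positive correlation the control mean rises more, so the bias runs against QC. With a negative one it favours QC.

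**6. Illustration B (assumed: loss in controls only; leavers differ from stayers by 1 SD).** Shift = f × 7.06, where f is the fraction lost.

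| Loss f | Shift (points) | Share of 5.4 |
|---|---|---|
| 10% | 0.7 | 13% |
| 20% | 1.4 | 26% |
| 30% | 2.1 | 39% |

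The consequence for the planned one-tailed test at 5%, assuming no true effect, 20 encounters per GP, 100 QC GPs and a shift that favours QC: SE = √[0.53 × 0.47 × (1 + 19 × 0.02)/20 × (1/100 + 1/n_c)], where n_c is the number of controls left.
- f = 10%: SE = 1.90 points, z = 1.645 − 0.706/1.90 = 1.27, rejection rate about 10%
- f = 30%: SE = 2.04 points, z = 1.645 − 2.12/2.04 = 0.61, rejection rate about 27%
- At a difference of 0.5 SD, the corresponding rates are about 7% and 13%.

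A shift in the other direction costs power instead.

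**7. Effect of adjusting for the GP's own baseline.** Both illustrations are unadjusted. If the underlying rate is stable, a change-from-baseline analysis removes the modelled shift. A regression on the observed baseline removes only the share m × 0.02/(1 + (m − 1) × 0.02), where m is baseline encounters per GP: 0.40/1.38 = 29% at m = 20 and 1.00/1.98 = 51% at m = 50. Neither deals with selection on how readily a GP changes practice.

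**The case against.** The strongest reply has four parts.

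- **The order is not stated.** Table 5 and Figure 3, which may show it, are not in the text at hand. This stands as a limit: the sequence is an inference, although nothing in the text points the other way.
- **Differential loss is not documented.** A reader might infer that disappointed controls will drop out and so flatter QC. The article does not say so. Education points are tied to completing the trial rather than to using QC (Ethical considerations), extraction is described as unobtrusive, and non-completers are contacted (Subject withdrawal). The QC arm faces more filters than control, namely the post-trial survey and the technical-difficulty exclusion, so net loss could be larger there. This also stands, and neither the direction nor the arm should be asserted. But a completion incentive does not equalise loss between arms, and the contact gathers reasons, not data.
- **The baseline values are safe.** A reader might infer that unmasked collection corrupts them. It cannot: they are existing records for the previous 12 months, extracted electronically. Only whether they are supplied can respond to the allocation.
- **The analysis uses adjusted data and compares baselines.** This may reduce the bias, by an amount that depends on the method (see the working), but it reaches only GPs who supplied data.

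It could also be said that reports by arm and sensitivity analyses belong in an analysis plan. Their absence here is not the point; the stated order of steps and the stated analysis set are.

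**Conclusion.** The point holds as a weakness in design. On the stated conditions, a GP can know the allocation before deciding whether to supply the data that determine inclusion in the primary analysis. The measures described do not close this gap.

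The size is unknown, because the article gives no non-provision rate and no information on how non-suppliers prescribe. Under the milder assumptions the bias is about 0.5 points, which is small. Under the stronger ones it is 0.7 to 2.1 points, enough to matter for a 5.4-point target. Every loss rate, correlation and leaver-stayer difference used is an assumption, and all figures precede adjustment for the GP's own baseline. The documents support neither a claim that the bias favours QC nor a claim that it has occurred.

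**What to change.** Release the assignment and the QC login only after the software is installed and the first retrospective extraction has been received. GPs who never install then leave without knowing their arm. The cost is a check on receipt before each release, a short delay to QC access, and some registrants lost before disclosure rather than after it. This removes allocation-driven loss at the first extraction, but not at 6 or 12 months.

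The article reports that the trial formally commenced in May 2005, so this order can no longer be applied to GPs already unmasked. For them, report the number supplying each extraction by arm, and run a sensitivity analysis that weights suppliers by the inverse of their estimated probability of supplying data. Base those weights on the registration and pre-trial survey data, which were collected before disclosure. This needs no new data, but it corrects only for differences that those variables capture.
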